## Abstract

**Background:**

A considerable number of minors in the United States are diagnosed with developmental or psychiatric conditions, potentially influenced by underdiagnosis factors such as cost, distance, and clinician availability. Despite the potential of digital phenotyping tools with machine learning (ML) approaches to expedite diagnoses and enhance diagnostic services for pediatric psychiatric conditions, existing methods face limitations because they use a limited set of social features for prediction tasks and focus on a single binary prediction, resulting in uncertain accuracies.

**Objective:**

This study aims to propose the development of a gamified web system for data collection, followed by a fusion of novel crowdsourcing algorithms with ML behavioral feature extraction approaches to simultaneously predict diagnoses of autism spectrum disorder and attention-deficit/hyperactivity disorder in a precise and specific manner.

**Methods:**

The proposed pipeline will consist of (1) gamified web applications to curate videos of social interactions adaptively based on the needs of the diagnostic system, (2) behavioral feature extraction techniques consisting of automated ML methods and novel crowdsourcing algorithms, and (3) the development of ML models that classify several conditions simultaneously and that adaptively request additional information based on uncertainties about the data.

**Results:**

A preliminary version of the web interface has been implemented, and a prior feature selection method has highlighted a core set of behavioral features that can be targeted through the proposed gamified approach.

**Conclusions:**

The prospect for high reward stems from the possibility of creating the first artificial intelligence–powered tool that can identify complex social behaviors well enough to distinguish conditions with nuanced differentiators such as autism spectrum disorder and attention-deficit/hyperactivity disorder.

**International Registered Report Identifier (IRRID):**

PRR1-10.2196/52205

## Introduction

### Background

Approximately 17% of minors in the United States aged 3 to 17 years have a diagnosis of ≥1 developmental or psychiatric conditions [1], with the true prevalence likely being higher because of underdiagnosis in rural areas and for minority populations [2]. Unfortunately, timely diagnostic services are inaccessible to a large portion of the United States and global population owing to cost, distance, and clinician availability. Digital phenotyping tools have the potential to shorten the time to diagnosis and bring diagnostic services to more people by enabling accessible evaluations. Although automated machine learning (ML) approaches for the detection of pediatric psychiatric conditions have garnered increased research attention in recent years, existing approaches use a limited set of social features for the prediction task and focus on a single binary prediction.

Many psychiatric conditions affecting adolescents contain overlapping etiologies and phenotypic characteristics. A major difficulty preventing the expansion of computational methods into the simultaneous prediction of multiple related conditions stems from heavy similarities between their phenotypes, creating barriers to achieving specificity and precision. Although some of the key overlapping and distinct features of these conditions are related to behaviors that can be automatically detected with ML methods, such as eye gaze patterns and facial emotion evocation, the majority are too complex for current ML techniques to classify precisely. For example, the degree to which a child enjoys participating in social games and interactions is one of the most salient behavioral features for autism spectrum disorder (ASD) diagnosis [3]. However, building an ML model for behavioral features is infeasible because of outliers and irrelevant, noisy features. These factors contribute to poor data generalization and increase the risk of overfitting. Furthermore, the constraints of existing benchmark data sets, characterized by a limited number of participants, pose challenges for deep learning (DL) models that thrive on substantial, diverse, and representative data to capture complex and nuanced features accurately [4]. By contrast, humans can naturally identify complex and nuanced behaviors by observing their peers. Crowdsourcing, or the use of distributed human workers toward a common goal, has the potential to bridge this gap by enabling rapid feature tagging of complex behaviors on demand. Although crowdsourcing has traditionally been used for public health studies and labeling ML training data, we plan to explore the incorporation of human labels into the feature extraction process. The intuition behind the proposed paradigm is that although nonprofessionals may be unable to directly identify psychiatric diagnoses from videos, many can tag behaviors that are relevant to a diagnosis.

We propose to develop a novel paradigm for accessible and scalable multicondition digital diagnostics of neuropsychiatric conditions by fusing traditional ML with novel human-in-the-loop crowdsourcing approaches. Although this approach (Figure 1) can be applied toward classification between any set of psychiatric conditions, we will focus on attention-deficit/hyperactivity disorder (ADHD) and ASD to maintain feasibility. The approach will comprise (1) developing gamified web applications to curate videos of social interactions adaptively based on needs of the diagnostic system, (2) innovative behavioral feature extraction techniques consisting of automated ML methods and novel crowdsourcing algorithms, and (3) ML models that classify several conditions simultaneously and that adaptively request additional information based on uncertainties about the data. We will collaborate with [name], who will provide domain expertise for pediatric developmental delays and methodological guidance for innovative biomedical data science solutions.

**Figure 1 figure1:**
[figure not shown]
Overview of the proposed crowd-powered diagnostic system comprising adaptive gamified data curation, behavioral feature extraction by both crowd workers and computational workflows, and machine learning models for multicondition classification that also output individual symptom estimates and dynamically query participants based on crowd ratings. Each of these 3 major steps is independent yet can be combined to produce a synergistic improvement in remote and accessible diagnostics for pediatric psychiatry. ADHD: attention-deficit/hyperactivity disorder.

The proposed project involves the integration of multiple data modalities for its diagnostic tasks, including from ML and from crowd workers. In our prior work, we have worked with several sources of information such as facial emotion [5,6], body movements [7,8], audio streams [9], and crowd worker ratings [10,11], all of which were used toward the singular goal of digital ASD diagnostics. For this protocol, we hypothesize that the complex and heterogeneous nature of the conditions that we plan to study requires multimodal data analysis to achieve a clinically acceptable level of performance, and this protocol will involve testing this theory.

### Related Work

Psychiatric conditions are widespread globally across demographic groups and geographical boundaries. The prevalence of ADHD is 2.5% in children and 5% in adults [3]. The prevalence of ASD is approximately 1% [3]. Approximately 50% to 70% of individuals diagnosed with ASD also have comorbid ADHD. Access to diagnostics, and therefore care, is limited for populations with low income or large geographic distances from clinicians. Although diagnostic modalities based on biomarkers are promising, they can be inaccessible to underserved populations. By contrast, a large and rapidly expanding portion of the global population has access to digital devices. As psychiatric conditions are fundamentally diagnosed based on behaviors, digital methods to measure behavior have the potential to bring diagnostic services to populations that have been traditionally neglected in health care.

A psychiatrist’s diagnostic evaluation process involves identifying ≥1 condition from a large set of possibilities defined by the Diagnostic and Statistical Manual of Mental Disorders, Fifth edition (DSM-5). However, current approaches to digital diagnostics tend to focus on binary predictions. A major bottleneck complicating the pursuit of multiclass psychiatric diagnostics is that behavioral conditions often have overlapping presentations (Table 1), severely complicating the use of purely automated methods.

**Table 1 table1:** Overlap of a small subset of the core behavioral symptoms of ASD^a^ and ADHD^b^. Overlap is determined according to the DSM-5^c^ diagnostic criteria [3].

Behavioral symptom	ADHD	ASD
Difficulty with social skills	✓	✓
Concentration issues	✓	
Hyperfixation	✓	✓
Restrictive and repetitive behaviors		✓
High distractibility	✓	
Impulsivity	✓	
Hyperactivity	✓	

^a^ASD: autism spectrum disorder.

^b^ADHD: attention-deficit/hyperactivity disorder.

^c^DSM-5: Diagnostic and Statistical Manual of Mental Disorders, Fifth edition.

In addition, each condition is heterogeneous, and all defining behavioral symptoms do not have to be present to warrant a diagnosis. Psychiatric conditions can either be comorbid (eg, ADHD and ASD) or not (eg, only ADHD or only ASD), creating a diagnosis space that scales combinatorially with each additional condition considered. For feasibility, we will only study 2 conditions to maintain a reasonably sized output space of 4.

The proposed research addresses a critical need in the field of pediatric neuropsychiatric diagnostics, focusing on the challenges posed by the prevalence of developmental and psychiatric conditions among minors in the United States. Current diagnostic practices face limitations in accessibility, particularly concerning cost, distance, and the availability of clinicians [10,12-14]. The *Background* section highlights the potential of digital phenotyping tools to overcome these challenges and expedite the diagnostic process through ML approaches. The field of digital phenotyping is vast and broad. A nonexhaustive list of National Institutes of Health–funded projects for developmental diagnostics includes the work by Guillermo Sapiro (NIH grant number R01MH120093) developing active closed-loop data collection for gaze and motor features for ASD as well as ADHD [15-22], work by James Rehg (NIH grant number R01MH114999) modeling nonverbal communication in atypical and typical development [23,24], work by Robert Schultz (NIH grant number R01MH118327) involving diagnostic computer vision analyses of motor movements displayed in videos of dyadic social interactions involving children with ASD [25], and work by [name] (NIH grant number R01LM013364) exploring the use of mobile games to acquire computer vision data for DL prediction of individual ASD-related behaviors [26-41].

Previous studies [4,12,42,43] have recognized the potential of ML techniques for detecting pediatric psychiatric conditions. However, a notable limitation of the existing approaches is their reliance on a limited set of social features for prediction tasks, often concentrating on a single binary prediction. For instance, in 2019, Carette et al [12] meticulously analyzed eye-tracking scanpath data using preprocessing procedures such as feature extraction via principal component analysis. The paper delineates comprehensive guidelines for the acquisition of the scanpath image data set. ML models were implemented, including support vector machine, logistic regression, random forest, and artificial neural network with diverse layers. The outcomes underscored the identification of a Childhood Autism Rating Scale score threshold of ≥36 as indicative of severe ASD. Notably, the single-layer artificial neural network model exhibited an improved area under the curve, outperforming support vector machine, which attained 77%. Despite the noteworthy findings, the study conscientiously recognized certain limitations, including a confined participant pool and shorter video scenarios, suggesting avenues for prospective investigations. This limitation raises concerns about the specificity and precision of these models, particularly when dealing with the overlapping etiologies and phenotypic characteristics inherent in many psychiatric conditions affecting adolescents [44].

The literature [14] underscores the complexity of overlapping psychiatric conditions, such as ADHD and ASD, and the challenges in achieving specificity and precision in their simultaneous prediction. Key behavioral features, such as eye gaze patterns and facial emotion evocation, present opportunities for automated ML methods, but the majority remain too complex for precise classification [10]. For example, a study [45] centered on analyzing eye-tracking image data using a clustering approach with 2 distinct algorithms, K-means and an autoencoder. The findings revealed that 33% of individuals were categorized into cluster 1, indicating the presence of ASD, whereas a higher prevalence of 85% was observed in cluster 2. However, the study lacks clarity on the specific feature extraction technique and parameter settings applied during the clustering process. Therefore, our study introduces a novel paradigm that integrates traditional ML with human-in-the-loop crowdsourcing approaches to address the limitation of feature annotation. The motivation behind this paradigm lies in the belief that although nonprofessionals may struggle to identify psychiatric diagnoses directly, they can effectively tag behaviors relevant to a diagnosis. This shift toward a crowdsourced, human-annotated feature space is a novel approach in the context of pediatric neuropsychiatric diagnostics.

In addition, ML models incorporating both human-annotated and automatically extracted features are hypothesized to outperform models using only 1 type of feature; there is a notable gap in the literature regarding the integration of human-annotated features through crowdsourcing for the specific purpose of enhancing diagnostic accuracy in pediatric psychiatry [4,42,46]. Mauro et al [13] introduced a model to extract sensory features from consumer feedback reviews, considering user preferences and compatibility information. The efficacy of their model was assessed across individuals considered autistic and neurotypical through integration into the recommendation algorithm. However, because the perception of places is inherently subjective, there exists a potential for bias in the feature values derived from explicitly crowdsourced data. Consequently, the authors recommended a comprehensive evaluation of the features through multimodal analysis to enhance the precision and accuracy of the proposed algorithm.

Our proposed research protocol fills a critical gap in the literature by combining automated ML methods with innovative crowdsourcing algorithms, aiming to create a diagnostic system with greater discriminative power than previously achievable in precision psychiatry.

## Methods

### Overview

In contrast to prior inspirational National Institutes of Health–funded efforts and others like them, we propose an approach to digital phenotyping that expands the possible feature vectors used to classify psychiatric conditions with complex and nuanced social features that only humans can identify using a novel *crowd-powered precision diagnostics* approach. The primary high-risk and high-reward differentiators from prior work are (1) the incorporation of a novel crowdsourcing pipeline into a precision diagnostic system to enable quantification of more complex social features, (2) the adaptive querying of the participant in question within a 2-player game-based system using active learning algorithms that exploit crowdsourced responses, and (3) the differential diagnosis of ASD and ADHD simultaneously. Differentiators (2) and (3) would not be possible without (1). The addition of targeted crowdsourcing into the diagnostic process creates several technical challenges that we will address, including automating the preservation of privacy of participants, efficiently and intelligently quantifying the behavioral feature–tagging ability of crowd workers, and creating algorithms for dynamically assigning workers to new data streams and tasks. Although prior projects have attained successful performances >90% using purely automated DL approaches to differentiate ASD from neurotypical peers [47], our preliminary data show that human-in-the-loop crowdsourced feature tagging of targeted behavioral features results in classification sensitivity, specificity, and accuracy >95%, even when privacy-preserving alternations are made to the video streams [42,48,49]. We hypothesize that incorporating both human observations, which are beyond the current and foreseeable abilities of ML, into the feature extraction process will provide enough social information for automated models to classify each condition using the same video data.

We hypothesize that diagnostic ML models that incorporate both human-annotated features acquired through crowdsourcing (to generate a complex feature space with respect to social human behavior) and automatically extracted features (to provide objectivity when possible) will outperform models that use only automatically extracted features or only human-provided features, as there will likely be nonlinear interactions between features. This complex feature space will allow the classification model to simultaneously distinguish 4 possible outcomes: only ASD, only ADHD, both ASD and ADHD, or neither condition. To support efficient and reliable feature tagging by workers, we will develop novel crowdsourcing algorithms for quantifying the behavioral tagging strengths and weaknesses of each worker. The algorithms will dynamically assign workers to tasks based on their tagging history. We will alter each video to provide privacy protection for the participants while still allowing reliable tagging. To facilitate the acquisition of sufficiently structured data, we will develop a broadly accessible gamified web platform for curating socially enriched video and audio clips in a targeted manner. We will use active learning algorithms to adaptively query for additional data in cases where the presence of a particular symptom is unclear from the current set of ML features and crowdsourced ratings. Each of these innovations (crowdsourcing algorithms, privacy-preserving video alterations, gamified social data capture systems, and active learning algorithms to dynamically query needed data), although useful for the field of precision psychiatry individually, will be combined to create a novel diagnostic system with greater discriminative power than previously possible.

Achieving the precision required to distinguish between ASD, ADHD, both ASD and ADHD, or neither from videos of social interaction using ML at clinically acceptable levels requires a complex social feature space that is not necessarily impossible but highly infeasible with purely automated methods. In contrast, untrained human annotators can identify nuanced social features but are prone to error because of the subjective nature of the task. Combining features extracted by both nonexpert human raters and computational programs can enable precise diagnostics and quantification of behaviors by creating a rich diagnostic feature space. There are several challenges to accomplishing targeted crowdsourcing in a precision health context, which we will address, including privacy preservation, quantifying crowd worker capabilities, and developing algorithms for matchmaking crowd workers with incoming data streams. The rich social feature space provided by crowdsourcing enables improvements to the other aspects of the digital behavioral diagnostics pipeline, including the adaptive assignment of participants to data collection games using active learning crowdsourcing metrics. Although we will focus on ASD and ADHD in particular, the crowd-powered methods we will develop have the potential to benefit diagnostics for any condition primarily evaluated through behavioral observation.

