#### Participant Recruitment and Management

We plan to recruit a total of 400 study participants, comprising 100 individuals formally diagnosed with ADHD, another 100 diagnosed with ASD, a further 100 diagnosed with both ASD and ADHD, and 100 individuals evaluated and confirmed to not have any socially related psychiatric conditions. Our inclusion criteria are as follows: (1) adolescents aged between 14 and 18 (inclusive) years and (2) formally evaluated for ADHD and ASD by a licensed clinician with available documentation. The selection of the final 400 participants that comprise our core data set will be based on the personal information that participants are asked to disclose. Such metadata will be used to ensure a data set that is balanced with respect to race, ethnicity, and gender. The number of participants is based on testing the ability of our system to discriminate between groups of participants. As these groups are balanced, we set the prevalence for binary classification between each condition to 50%. Following a CI of 95%, an estimated theta of 95% [42,48,49], and a width of 15%, the sample size to compute the area under the receiver operating characteristic curve (AUROC) should be 37 [54]. Considering that we have 400 participants, with 100 participants per group, this enables us to follow a common 60:20:20 (train, validation and test ratio respectively) randomized split on the data. That is, we have a sample size (test set) of 40 participants to verify the system’s ability to discriminate between the neurotypical participants and the participants who were diagnosed with either ASD, ADHD, or comorbid ASD and ADHD.

Although formal and well-established methods to perform power calculations for ML analyses have yet to be established, most digital diagnostics studies for conditions such as ASD include <100 participants per class in binary classification [47]. We aim to maintain a similar sample size per diagnostic category. The digital social experiences will be delivered to study participants for 15 minutes each day for a 3-week duration, with a single game out of the 7 possible delivered each day. At least 3 distinct 15-minute sessions will be collected per game for each participant, allowing for comparisons across days for analysis of within-peer consistency.

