#### Evaluation

The diagnostic ML model will be evaluated using balanced classification metrics including AUROC, area under the precision-recall curve, balanced accuracy, precision, recall (sensitivity), *F*_1_-score, and specificity. Performance and CIs will be derived through Monte Carlo cross-validation, with each data split consisting of 300 participants in the training set, 50 participants in the validation set, and 50 participants in the test set. All splits will contain a balance with respect to the 5 diagnostic classes, age, gender, race, and ethnicity.

To evaluate the effectiveness of the active learning querying system, we will run post hoc simulations comparing the random selection of new data against targeted requests using active learning. We will train the classification system with 12 sessions of data, hold out the remaining 9 sessions, and plot the performance of each metric against the number of additional samples acquired using both active learning and random selection of data segments.

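### The fused-versus-single-source hypothesis has no matching comparison in the diagnostic evaluation, and n=37 covers only the precision of one AUROC

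*Protocol article*

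**What the plan says.** The comparative hypothesis appears twice. Related Work says "ML models incorporating both human-annotated and automatically extracted features are hypothesized to outperform models using only 1 type of feature". Methods, Overview says that models with both feature types "will outperform models that use only automatically extracted features or only human-provided features". The Introduction, after Figure 1, puts forward the related idea that these conditions need multimodal data for acceptable performance, and adds that "this protocol will involve testing this theory". It does not say how.

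The evaluation under Multicondition Diagnostics With Adaptive Input Querying reads "The diagnostic ML model will be evaluated using balanced classification metrics including AUROC", followed by other single-model metrics, and then "Performance and CIs will be derived through Monte Carlo cross-validation", with splits of 300, 50 and 50 participants. It also compares active learning with random selection of new data.

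Participant Recruitment and Management derives the sample size thus: "Following a CI of 95%, an estimated theta of 95% [42,48,49], and a width of 15" (per cent), with 50% prevalence, giving 37. It then describes a 60:20:20 split of 100 per group and a test set of 40 for discriminating between groups.

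**The concern.** A hypothesis that one model outperforms two others concerns two differences, and evidence for it has to come from estimates of those differences. The evaluation and the sample-size argument both address a different quantity: how well one model discriminates, and how precisely one AUROC is known. The study could follow its text exactly, report a good AUROC for the fused model, and have no planned evidence on whether crowdsourced features add to automated ones or the reverse. A comparison improvised afterwards would leave the comparator, metric, interval method and success rule to be chosen once results are known. If it were made on one test set of the stated size, a modest real gain would usually be missed.

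**Working it through.** **1. Hypothesis set against named comparisons.**

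| Comparison in the article | Section | Tests fused v single-source diagnosis? |
|---|---|---|
| Behavior-level ML model v crowd ratings alone | Multicondition Diagnostics, Description | No: per behavior, target is the clinician rating |
| Active learning v random selection of data | Multicondition Diagnostics, Evaluation | No |
| Privacy conditions, deviation from clinician answers | Feature Extraction, Evaluation | No |
| Diagnostic model: AUROC and other metrics | Multicondition Diagnostics, Evaluation | No: one model, no difference |

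**2. Reproducing 37.** Inputs from Participant Recruitment and Management: A = 0.95, total width 0.15, 95% interval, equal groups. Hanley-McNeil variance:

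SE² = [A(1−A) + (n₁−1)(A/(2−A) − A²) + (n₀−1)(2A²/(1+A) − A²)] / (n₁n₀)

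- A(1−A) = 0.0475
- A/(2−A) − A² = 0.9048 − 0.9025 = 0.0023
- 2A²/(1+A) − A² = 0.9256 − 0.9025 = 0.0231
- Setting 2 × 1.96 × SE = 0.15 with n₁ = n₀ gives N = 36.36, rounded up to 37.

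The width is 0.149 at 37, 0.143 at 20 v 20 and 0.044 at 200 v 200. The figure is correct for its purpose. It contains no second model, difference, power or between-model correlation. The planning value of 0.95 cites the same references as the crowdsourced result above 95% in Methods, Overview, so no gain over crowd-only features is built in.

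**3. What a comparison would need.** The article gives no AUROC gap, power or correlation for this comparison, so the values below are assumptions, shown over a range. For two AUROCs on the same participants:

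SE(diff)² = s₁² + s₂² − 2·r·s₁·s₂; power = Φ(diff/SE(diff) − 1.96)

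Example, 0.95 v 0.90 with 20 v 20: s₁ = 0.0364, s₂ = 0.0514.
- r = 0: SE = 0.0630, power = Φ(0.79 − 1.96) = 12%.
- r = 0.7: SE = 0.0367, power = Φ(1.36 − 1.96) = 28%.

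Formula results, with r (the correlation of the two AUROC *estimates*) from 0 to 0.7:

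| Assumed AUROCs | 20 v 20 | 25 v 25 | 200 v 200 |
|---|---|---|---|
| 0.98 v 0.95 | 10-21% | 12-25% | 61-96% |
| 0.95 v 0.90 | 12-28% | 14-33% | 72-99% |
| 0.95 v 0.85 | 28-60% | 34-70% | 99-100% |
| 0.95 v 0.815 | 41-76% | 50-85% | 100% |

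The 0.815 is the audio-only AUROC in Table 3 (binary ASD), a low-end value for a multi-feature automated model. 20 v 20 is one pair of groups under the 60:20:20 split; 25 v 25 is ASD yes/no in the 50-person test set. If ASD yes/no used all 80 test participants of the 60:20:20 split (40 v 40), power for 0.95 v 0.90 would be 20-49%.

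**4. Check by simulation.** Binormal scores, paired DeLong test, two-sided 5%, correlation of the *scores* 0.5-0.7:

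| Assumed AUROCs | 20 v 20 | 25 v 25 | 200 v 200 |
|---|---|---|---|
| 0.95 v 0.90 | 11-15% | 17-21% | 94-100% |
| 0.95 v 0.815 | 58-75% | 71-85% | about 100% |

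For 0.98 v 0.95 at 20 v 20 the simulation gives only 3-5%, below the formula, because the normal approximation is poor so near 1. The 200 v 200 columns treat out-of-fold predictions for all 400 as independent.

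**The case against.** The strongest reply is that the stated Objective is to build the system and predict both conditions, that the sample-size paragraph says it sizes for discrimination between groups, and that a precision-based size is legitimate for that. A condensed article may also leave ablation fits and paired tests to a fuller document. The first part stands: no hypothesis is labelled primary, so a reader might infer that the study cannot answer its main question, and the text does not support that label. The second part stands only in part. Details of a paired test can wait, but the article does fix its diagnostic evaluation and spells out other comparisons, and the one it hypothesizes twice is not among them. Nothing says single-source models will not be fitted.

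Two further inferences are tempting and should not be drawn.

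- The half-width of 0.075 exceeds the 0.05 between 0.95 and 1, so a reader might conclude that no gain could be resolved. That does not follow. The precision of a paired difference depends on the paired standard error, and the 0.05 limits the gain only if the single-source model is already at 0.95.
- A reader might conclude that participants outside one test set go unused, or that the pairing is thrown away. Monte Carlo cross-validation rotates participants through the test set, and nothing says models would be compared on different people. The 20 v 20 and 25 v 25 figures therefore describe one test set, not the whole scheme.

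It is also fair that power depends on the gap. The authors regard purely automated methods as highly infeasible for this task, so they may expect a large gap for that arm. The low figures bear mainly on small gaps, such as the crowd-only comparison may present.

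**Conclusion.** The point holds in this form: the article hypothesizes that fused models beat both single-source models, but its stated evaluation yields no estimate of either difference, and n=37 is a correct precision figure for a single AUROC that lends no support to the comparison. That mismatch is read directly from the text and needs no assumption.

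Its size does. With one test set of 40 to 50, a gain from 0.90 to 0.95 would be detected about 11-21% of the time at score correlation 0.5-0.7 (12-33% by formula with r from 0 to 0.7). A gap as large as 0.815 to 0.95 would be detected about 58-85% of the time. With all 400 contributing, power for 0.95 v 0.90 is about 94-100%, or 72% by formula if r is 0. Power to beat both comparators cannot exceed power to beat the harder one. So the defect lies in the unstated comparison and the reach of the sample-size claim, not necessarily in the recruitment target. It should be corrected before the diagnostic analysis starts.

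**What to change.** In the diagnostic Evaluation section:

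- Name three diagnostic models (automated-only, crowd-only and fused) and fit them on identical participant splits.
- Report the paired AUROC difference of fused minus each single-source model from participant-level out-of-fold predictions.
- Take the interval by resampling participants rather than splits. Monte Carlo test sets overlap, so the spread across splits is not a valid interval for the difference.
- Claim the hypothesis only if fused beats both comparators.

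In Participant Recruitment and Management, state that 37 covers the precision of a single AUROC and not this comparison.

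The cost is two further model fits and some analysis work. Both feature types are already collected on the same participants, so no extra recruitment is needed.
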